### Definitions

All variables in the ETNA-VTE-Europe study are defined as similarly as possible to those in the PREFER in VTE and Hokusai-VTE studies to permit close comparison of results [6, 13–15]. However, the feasibility of this is somewhat limited by the non-interventional setting. A comparison of the most important variable definitions is provided in Table 2. Permanent edoxaban discontinuation is defined as cessation of edoxaban treatment within the follow-up period.

**Table 2 Tab2:** Definitions of VTE and bleeding events in ETNA-VTE-Europe, PREFER in VTE and Hokusai-VTE studies

	ETNA-VTE-Europe	PREFER in VTE [13, 14]	Hokusai-VTE [6, 15]
**VTE**			
Baseline	Confirmed first time/recurrent distal/proximal acute symptomatic DVT and/or PE	Confirmed first time/recurrent distal/proximal acute symptomatic DVT and/or PE	Confirmed first time/recurrent **proximal** acute symptomatic DVT and/or PE
Recurrent (during study)	VTE, as adjudicated by an independent CEC	DVT or PE, **as diagnosed by investigator** (**not adjudicated)**	DVT, new non-fatal symptomatic/fatal PE, as adjudicated by an independent CEC^a^

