### Statistical analysis

Owing to the non-interventional study design, all ETNA-VTE-Europe data analysis will be explorative and descriptive only. In addition to the Europe-wide analysis, safety and effectiveness data will be presented for each individual country and region (Austria, Switzerland and Germany [DACH]; the United Kingdom and Ireland [UK/IE]; Belgium and the Netherlands [BE/NL]; and Italy). Comparisons between patients in particular edoxaban exposure categories (current use, recent use [within the last 3 days], and past use [> 3 days ago], as well as use within the last 30 days) will also be performed, with outcome data additionally presented for all patients permanently discontinuing edoxaban. Furthermore, subgroup analyses comparing patients with/without the following baseline characteristics are planned: renal impairment, hepatic impairment, DVT only (vs. PE with/without DVT), age ≥ 75 years, male gender, initial 30 mg edoxaban dose (vs. 60 mg), and active cancer.

To provide context to our results, the outcomes of ETNA-VTE patients will be appraised relative to those of PREFER in VTE patients treated with a DOAC, PREFER in VTE patients treated with a vitamin-K antagonist (VKA), Hokusai-VTE patients treated with edoxaban, and Hokusai-VTE patients treated with warfarin. These evaluations will be performed on an entirely visual basis, with no joint statistical models planned. Given the one-year follow up of the PREFER in VTE and Hokusai-VTE studies, only 12-month data from ETNA-VTE-Europe will be considered for these purposes [12, 13].

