*Legend*: Y, year; M, month; DVT, deep vein thrombosis; FU, follow-up; PE, pulmonary embolism; DOAC, direct oral anticoagulant; VTE, venous thromboembolism; TIA, transient ischaemic attack; PASS, post-authorisation safety study; Q4, fourth quarter; MI, myocardial infarction; SE, systemic embolism; CV, cardiovascular; VKA, vitamin-K antagonist, C, completed; O, ongoing, TEAE, treatment-emergent adverse events. Important differences are highlighted in **bold**. ^a^Swiss sites: February 2015. ^b^Precise number unknown

Current evidence for the safety and efficacy of edoxaban largely emanates from the phase III Hokusai-VTE clinical trial [6]. A key limitation of this study was the exclusion of patients with characteristics encountered in routine clinical practice, such as those with isolated distal symptomatic DVT, a creatinine clearance of < 30 mL/min, and significant liver disease. Consequently, the effectiveness and safety in some clinical subgroups to edoxaban remain unrepresented and uncharacterised. Data gathered from the ETNA-VTE-Europe study with minimal selection criteria will address this knowledge gap, with several pertinent subgroup analyses already planned. The gathered data will also provide a snapshot of the types of patients being prescribed edoxaban, the doses used, and the durations of treatment in a real-life setting. This will permit appraisal of the appropriateness of such therapeutic decisions as well as acting as a marker for evaluation of subsequent trends of prescription.

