### Potential limitations

As a prospective, non-interventional registry that aims to represent everyday occurrence and management of VTE, the stringent inclusion/exclusion criteria, physician/patient blinding, and site/protocol standardisation that typify RTCs do not apply. This introduces the possibility for biases that are difficult to avoid, measure or correct for. In particular, heterogeneous timing and length of edoxaban exposure may prove problematic for the interpretation of results, thought this will be taken into consideration at data analysis. Furthermore, in such a large-scale study, some incompleteness, insufficient detail, or inaccuracy of patient data is unavoidable; however, measures such as the careful design of case report forms and data monitoring/verification aim to minimise such occurrences. Despite the inherent limitations associated with observational registries, the all-inclusive nature of ETNA-VTE Europe may be seen as an advantage for obtaining a realistic snapshot of the clinical climate, with two-wave recruitment potentially allowing changes in treatment behaviour over time to be elucidated. Finally, while the single-arm nature of the study means that direct comparisons with other anticoagulants will not be possible, close accordance between the designs of PREFER in VTE and ETNA-VTE Europe should permit a reasonable appraisal of outcome differences.

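### The 12-month recurrence display sets adjudicated ETNA events beside unadjudicated PREFER events, and the Hokusai display adds a separate case-mix difference of unknown direction

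*Protocol article*

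**What the plan says.** Methods, Definitions, Table 2 gives three definitions of recurrence during the study:

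- ETNA-VTE-Europe: "VTE, as adjudicated by an independent CEC".
- PREFER in VTE: DVT or PE "as diagnosed by investigator", marked in bold as not adjudicated.
- Hokusai-VTE: "DVT, new non-fatal symptomatic/fatal PE, as adjudicated by an independent CEC".

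For the index event, ETNA and PREFER share one wording, "Confirmed first time/recurrent distal/proximal acute symptomatic DVT and/or PE". Hokusai has "Confirmed first time/recurrent proximal acute symptomatic DVT and/or PE". The Discussion adds that Hokusai left out patients with "isolated distal symptomatic DVT, a creatinine clearance of" less than 30 mL/min, and those with significant liver disease.

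Under Objectives and outcome measures, these contrasts serve a secondary objective: how effective and safe edoxaban is relative to other anticoagulants. Statistical analysis names four comparator groups (PREFER DOAC, PREFER VKA, Hokusai edoxaban, Hokusai warfarin), limits the contrast to 12 months, and states: "These evaluations will be performed on an entirely visual basis, with no joint statistical models planned". Potential limitations concludes that "close accordance between the designs of PREFER in VTE and ETNA-VTE Europe should permit a reasonable appraisal of outcome differences".

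**The concern.** In the PREFER contrast the outcome is counted differently on the two sides. A recurrence that a site reports counts in PREFER as it stands, but counts in ETNA only once the committee has accepted it. With no model behind the display, nothing later in the analysis can correct for this. The display is the analysis, and a reader would put the gap down to the drug.

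The Discussion explains the choice of PREFER by its bleeding definitions, assessment times and patient numbers. Recurrence, the primary outcome of ETNA, is not among the reasons. Potential limitations then leans on agreement of the designs without mentioning adjudication.

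In the Hokusai contrast the outcome is adjudicated on both sides, but the populations differ. The planned subgroups include DVT only versus PE with or without DVT, renal impairment and hepatic impairment. None separates distal from proximal DVT, so no display described in the article shows ETNA patients who match Hokusai on the index event.

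**Working it through.** **1. Which mismatch belongs to which comparator (Table 2)**

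| Contrast | Recurrence counted alike? | Index-event population alike? |
|---|---|---|
| ETNA vs PREFER | No: adjudicated vs not adjudicated | Yes: distal or proximal in both |
| ETNA vs Hokusai | Yes as to adjudication: a committee in both | No: Hokusai has proximal DVT and/or PE only |

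On these two items, each comparator carries one difference.

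**2. The plan's own precision, as a yardstick**

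Inputs from Sample size calculations: p = 0.08 (18-month recurrence), r = 0.15 (relative precision), two-sided 95% CI.

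n = 1.96² × (1 − p) / (p × r²) = 3.8415 × 0.92 / (0.08 × 0.0225) = 1963.4, so 1964. This reproduces the stated figure. Enrolment of 2700 less 25% leaves 2025, which is enough. The half-width at 1964 patients is 1.2 percentage points. The point raised here leaves the sample size unaffected.

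**3. PREFER: effect of adjudication alone**

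Suppose the drugs are equally effective and sites report at the same rate p in both studies. Let c be the fraction of reported ETNA events that the committee confirms, with no events added. Then:

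- ETNA displayed rate = c × p
- apparent ratio = c
- apparent difference = p × (1 − c)

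The documents do not give c, so the table shows a range of assumptions. The 8% is the plan's 18-month figure; the contrast is made at 12 months, so an assumed 4% is shown as well.

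| c (assumed) | Apparent ratio | Difference at 8% | Difference at 4% (assumed) |
|---|---|---|---|
| 0.95 | 0.95 | 0.4 points | 0.2 points |
| 0.90 | 0.90 | 0.8 points | 0.4 points |
| 0.85 | 0.85 | 1.2 points | 0.6 points |
| 0.80 | 0.80 | 1.6 points | 0.8 points |
| 0.70 | 0.70 | 2.4 points | 1.2 points |

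The ratio does not depend on p. At c = 0.85 the distortion is 15% relative, or 0.08 × 0.15 = 1.2 points at the 8% rate, which equals the planned precision. A lower c exceeds it. Recruiting more patients does not shrink it. Counting investigator-reported events on both sides removes it.

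**4. Hokusai: effect of case mix**

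Let d be the share of ETNA patients with isolated distal DVT and R_d their recurrence risk relative to the rest. Let h be the share of other patients whom Hokusai excluded and R_h their relative risk. All four are assumptions.

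Ratio = (1 − d + d × R_d) × (1 − h + h × R_h)

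- Distal only, d = 0.10 to 0.30, R_d = 0.5 to 1.0: lowest 1 − 0.30 + 0.30 × 0.5 = 0.85; highest 1.00.
- Adding h = 0.10 with R_h = 2 to 3: lowest 0.85 × 1.1 = 0.935; highest 1.00 × 1.2 = 1.20.

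Overall the range is 0.85 to 1.20, which includes 1. The sign is not fixed.

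**The case against.** The strongest reply is that nothing is hidden. Table 2 prints both differences in bold, and Definitions concedes that alignment is limited. Statistical analysis calls all analysis explorative and descriptive. The sentence in Potential limitations that relies on agreement of the designs opens by saying that a single-arm study cannot compare drugs directly. Detailed table layouts may also stand in the full protocol or analysis plan.

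This lowers the weight of the point but does not remove it. A descriptive display still has to count the same event on both sides. The limited alignment is attributed to the non-interventional setting, yet PREFER is observational too; the mismatch arises because ETNA adds adjudication. The article then states that outcome differences can reasonably be appraised, which Table 2 does not support for recurrence.

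Other parts of the reply stand in full, and they rule out stronger readings that a reader might infer:

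- *That all the planned contrasts favour edoxaban by definition.* PREFER also enrolled distal DVT and Hokusai is also adjudicated, so neither comparator has both differences. For Hokusai the documents do not say that distal DVT recurs less often, and the other excluded patients could push the rate the other way. One Hokusai contrast is edoxaban against edoxaban and cannot favour the drug over another.
- *That adjudication can only remove events.* The article does not describe the committee's procedures. It might, for example, reclassify a death as VTE-related. A lower ETNA rate is plausible but conditional.
- *That a Hokusai-like subset would isolate the effect of setting.* Country, period and exclusions not listed in the article would still differ. A creatinine-clearance filter could also select on data availability, because laboratory values are recorded only if assessed and missing observations are omitted.

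**Conclusion.** The point holds for PREFER recurrence: the plan sets adjudicated beside unadjudicated events, and the stated reliance on similar designs leaves this out. If the committee rejects some reports and adds none, the contrast tilts towards edoxaban by the confirmation fraction: a ratio of 0.70 to 0.95 for assumed confirmation of 70% to 95%. At 85% or below, the distortion is at least as large as the 15% relative precision planned for the 18-month primary outcome. No confirmation fraction is documented, so these figures show sensitivity and do not estimate the bias.

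For Hokusai, what holds is narrower. The populations differ in the index event, no planned subgroup described in the article aligns them, and the direction is unknown (0.85 to 1.20 under the assumptions shown).

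The primary analysis and sample size are untouched. What is affected is the secondary objective of placing edoxaban relative to other anticoagulants. The distortion is avoidable and should be dealt with before the displays are built.

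**What to change.** 1. In the PREFER displays, show ETNA investigator-reported (pre-adjudication) recurrences with a 95% CI alongside the adjudicated ones, and name the former as the like-for-like comparison.
2. In the Hokusai displays, keep adjudicated events and show two ETNA columns with 95% CIs: all patients, and those with index proximal DVT and/or PE. Describe the second as a partial alignment of case mix, not as isolating the effect of setting.
3. In Potential limitations, name the adjudication difference from PREFER and the index-event difference from Hokusai, and qualify the statement about agreement of the designs.

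The cost is a few extra table columns. Table 1 has sites record the timing and diagnosis of recurrences and the diagnostic details of the index event, so both inputs should already be in the database. The sponsor should confirm that the pre-adjudication report is retained and that distal and proximal DVT can be told apart. The PREFER display may look less favourable to edoxaban as a result.

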**Bleeding**			
Major	Overt: fatal, symptomatic in a critical area/organ, causing a ≥ 2 g/dL fall in haemoglobin and/or ≥6.0% fall in haematocrit^b^	Overt: fatal, symptomatic in a critical area/organ, causing a ≥ 20 g L^−1^ fall in haemoglobin or **transfusion of ≥ 2 units of whole blood or red cells**^**b**^	Overt: fatal, occurs in a critical site, associated with a ≥ 2 g/dL decrease in haemoglobin or requires a **transfusion of ≥ 2 units of blood**
Life-threatening	Major: intracranial or associated with haemodynamic compromise requiring intervention	**Not specified**	**Not specified**
CRNM	Overt: requires medical attention but does not fulfil major bleeding criteria^b^	Overt: does not meet major bleeding criteria but prompts a clinical response (**hospital admission/physician-guided treatment/change in antithrombotic therapy**)^**b**^	Overt: associated with the need for medical intervention, **contact with a physician, interruption of study drug, or discomfort/impairment of ADL,** but does not fulfil major bleeding criteria
Minor	Overt: other; does not fulfil the criteria for major/CRNM^b^	Overt: other; does not fulfil the criteria for major/CRNM^**b**^	**Not specified**

*Legend:* DVT, deep-vein thrombosis; PE, pulmonary embolism; VTE, venous thromboembolism; CRNM, clinically relevant non-major; CEC, clinical events committee; ADL, activities of daily living. ^a^Members unaware of treatment allocation. ^b^As defined by the International Society of Thrombosis and Haemostasis (2005) [11]. Items in **bold** reflect differences compared to ETNA-VTE-Europe

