### Documentation and assessment

Data for this study will be sourced from medical records and, when in line with routine clinical practice, from telephone calls between the patient and treating physician. As a non-interventional study, no patient contact, examinations, laboratory tests or procedures are compulsory, and will only be carried out at the discretion of the treating physician, as and when deemed appropriate and without registry influence. A standardised electronic case report form (eCRF) will be completed by the site shortly after enrolment and again after every interaction with a patient over the subsequent 18 months. The eCRFs will be uploaded to the secure, internet-based Medidata Rave EDC system.

Given that the edoxaban SmPC recommends 5 days of parenteral anticoagulation following VTE before starting edoxaban treatment [7], baseline is defined as the first day of heparin/fondaparinux administration after the index acute VTE event. The first data entry, which will be completed following enrolment and within 2 weeks of the index VTE, will include details of baseline patient characteristics, comorbidities, VTE-related parameters, past and current therapy, and other relevant assessments made according to site protocol (Table 1). Memory aids will be provided to all patients at enrolment, with space to record edoxaban-related treatment changes, use of concomitant medication, adverse events, hospitalisation, physician contact, and productivity loss. This aid can be used to assist with recall during subsequent visits/telephone calls, but are voluntary and will not be formally assessed. In each country, all patients will be followed until the last patient for that particular country has completed the 18-month documentation period, in line with EMA requirements. At this point, a last-patient-out (LPO) questionnaire, requesting a minimum of vital status, will be issued for each patient enrolled in the respective country.

**Table 1 Tab1:** Time points for data assessment

	Baseline*	1 month	3 months	6 months	12 months	18 months	Country-specific LPO
Eligibility criteria^(1)^	X						
Baseline characteristics^(2)^	X						
VTE-related parameters^(3)^	X	X^§^	X^§^	X^§^	X^§^	X^§^	
Edoxaban therapy^(4)^	X	X	X	X	X	X	
Concomitant anticoagulants	X	X	X	X	X	X	
Interventions	X	X	X	X	X	X	
Adherence to VTE therapy^(5)^	X	X	X	X	X	X	
Recurrent VTE^(6)^		X	X	X	X	X	X^†^
Other clinical events^(7)^	X	X	X	X	X	X	
Hospitalisation for cardiovascular disease^(8)^		X	X	X	X	X	

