An additional limitation of current studies is that data are only available for up to 12 months of edoxaban therapy [6]. Considering that a number of patients will require longer-term anticoagulation in clinical practice [8], those continuing edoxaban dosing beyond 12 months will find themselves in uncharted waters. The 18-month follow-up period planned for ETNA-VTE-Europe patients will provide clinicians and patients with valuable information regarding the safety and net clinical benefit of extended treatment. In particular, trends in rare ADRs such as liver events and major bleeding will be of interest, given their low frequency in the Hokusai-VTE trial [6]. Combination of ETNA-VTE-Europe data with those from the ETNA-AF-Europe sister study will provide an even larger population from which to assess these safety outcomes [10]. Thus, the present PASS is a responsible and important part of the early post-marketing phase, designed to address several of the knowledge gaps highlighted in the EMA risk-management plan for edoxaban [9].

The single-arm design of the ETNA-VTE-Europe study reflects its key aim of characterising the real-world safety and effectiveness of edoxaban. However, visually comparing our results to those from similar studies with different anticoagulants will help to provide perspective. To these ends, data from the recent PREFER in VTE real-world registry will be used to contextualise data from ETNA-VTE-Europe, selected for its comparable bleeding definitions, coinciding data assessment time points, and high patient numbers (3545 patients) [14]. This will allow us to gain an idea of the real-world safety and effectiveness of edoxaban relative to agents such as VKAs and other DOACs, not only in the overall population, but also in specific patient subsets, such as those with renal or hepatic impairment. Furthermore, several of the countries and regional delineations in ETNA-VTE-Europe (such as Italy, DACH and UK/IE) also feature in the PREFER in VTE study, enabling various approximate geographical comparisons [13]. A further evaluation of ETNA-VTE-Europe real-world results in the context of those from the Hokusai-VTE clinical trial will provide insight into the influence of stringent enrolment criteria and closer monitoring on edoxaban-related outcomes. This will indicate to what extent the encouraging findings from phase III studies can be expected to translate into clinical practice.

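### ETNA major bleeding omits the transfusion criterion that PREFER and Hokusai use and adds a haematocrit criterion, so the 12-month comparison is not like for like although the definitions are called comparable

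*Protocol article*

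**What the plan says.** **ETNA definition.** In Table 2, the ETNA cell for major bleeding lists four routes: fatal; symptomatic in a critical area or organ; a haemoglobin fall of at least 2 g/dL; and a haematocrit fall of at least 6.0%. The last two read "fall in haemoglobin and/or ≥6.0% fall in haematocrit". No transfusion route is listed.

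**Comparators.** The PREFER cell gives a haemoglobin fall of at least 20 g/L (the same threshold as 2 g/dL) or transfusion of at least 2 "units of whole blood or red cells". The Hokusai cell gives a 2 g/dL "decrease in haemoglobin or requires a" transfusion of at least 2 units. Neither lists haematocrit.

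**Marking of differences.** The legend says that items in bold "reflect differences compared to ETNA-VTE-Europe". Transfusion is bold in both comparator cells. Nothing marks the haematocrit difference.

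**Source.** Footnote b, "As defined by the International Society of Thrombosis and Haemostasis (2005", reference 11), is attached to both the ETNA and the PREFER wording. Objectives and outcome measures defines the bleeding components of the co-primary outcome by the same reference.

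**Claims about similarity.** The Definitions section says that variables were matched to the two comparators as closely as the non-interventional setting allows. The Discussion says that PREFER was "selected for its comparable bleeding definitions, coinciding data assessment time points, and high patient numbers".

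**Use.** Statistical analysis sets 12-month ETNA-VTE data beside PREFER and Hokusai by eye, with no joint model.

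**The concern.** Two wordings that differ in substance cannot both be the definition in one cited source. Either the ETNA cell or its footnote needs correcting, and a reader cannot tell which rule will classify major bleeding.

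The wording also matters in this setting. Under Documentation and assessment, "no patient contact, examinations, laboratory tests or procedures are compulsory", and Table 1 records laboratory values only if they were assessed. Both quantitative ETNA criteria depend on laboratory values, and no treatment-based criterion stands beside them. A bleed treated with 2 or more units that meets none of the four ETNA routes falls into CRNM, the category for overt bleeding that "requires medical attention but does not fulfil major bleeding criteria".

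At stake is the reading of major bleeding, which the Discussion singles out as an event of interest. A visual comparison has no model to adjust for different definitions, so a gap or a match between the studies could come partly from the definition.

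**Working it through.** **Plan's own figures.** The article gives no expected major-bleeding rate. Its safety precision figure reproduces: (2700 + 13,100) × 0.80 = 12,640, and 1.96 × √(0.01 × 0.99 / 12,640) = 0.173 points, the stated 0.17%. That figure belongs to the 18-month pool with ETNA-AF-Europe, not to the 12-month display beside PREFER and Hokusai.

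**Which events move.** Let A be bleeds that are fatal, at a critical site, or with the haemoglobin fall; T those with at least 2 units transfused; H those with the haematocrit fall.

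- ETNA major = A or H.
- PREFER and Hokusai major = A or T.
- In T but in neither A nor H: major in the comparators, CRNM in ETNA.
- In H but in neither A nor T: major in ETNA, not major in the comparators.
- In both T and H: major everywhere.

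**Net shift.** Let R be the major-bleeding rate under the comparators' definition, f the share of those bleeds that qualify only by transfusion, and g the haematocrit-only bleeds as a proportion of R. Then

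ETNA rate = R(1 − f + g), and shift = R(g − f).

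The sign depends only on whether f or g is larger, and the documents give neither.

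**Illustration.** Assumed ranges: R = 1% to 3%, f = 0 to 30%, g = 0 to 10%. At R = 2%:

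- f = 10%, g = 0: 1.8% (−0.2 points)
- f = 30%, g = 0: 1.4% (−0.6)
- f = 10%, g = 10%: 2.0% (no change)
- f = 5%, g = 10%: 2.1% (+0.1)

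**Against ETNA-VTE precision.** The 12-month evaluable number is not stated. The limits used are 2700 × 0.75 = 2025 (the 18-month dropout) and full enrolment of 2700. Half-width = 1.96 × √(R(1 − R)/n).

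| R | Range of shift (points) | Half-width, n = 2025 | Half-width, n = 2700 |
|---|---|---|---|
| 1% | −0.3 to +0.1 | 0.43 | 0.38 |
| 2% | −0.6 to +0.2 | 0.61 | 0.53 |
| 3% | −0.9 to +0.3 | 0.74 | 0.64 |

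At 1% the shift stays inside the half-width throughout. It exceeds the half-width only at the higher rates, and only when f exceeds g by more than about 20 percentage points (0.64/3 = 0.21 at R = 3%, n = 2700). A shift from the definition does not shrink as n grows.

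**The case against.** **The difference is disclosed.** Table 2 exists to show differences, and transfusion is in bold. The Definitions section warns that matching is limited, the analyses are declared descriptive, and Potential limitations rules out direct comparison with other anticoagulants. This stands in part. The haematocrit difference is unmarked, the effect on the comparison is not discussed, and the non-interventional setting alone does not explain the omission: Table 3 lists PREFER as observational too, and PREFER uses transfusion.

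**The article condenses a fuller protocol.** The ETNA cell could be an abbreviation. This is weak here, because bolding transfusion in both comparator cells asserts that ETNA lacks it. It does hold for data capture: the case report form is not shown, and Table 1 records interventions at every visit to 18 months, so transfusion units may already be collected.

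**Few events move.** This stands. A transfused bleed that meets any ETNA route stays major. Reclassified bleeds are still counted as CRNM, itself a component of the co-primary outcome, so total bleeding is unchanged.

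**A stronger reading.** A reader might infer that the co-primary safety rate is understated against both comparators, in edoxaban's favour, by as much as the stated 0.17% precision. The documents do not support this. The co-primary analysis is an 18-month pool in which about 13,100 of 15,800 patients come from ETNA-AF-Europe, whose bleeding definition is not shown, and no comparison of that pool with PREFER or Hokusai is planned. The haematocrit criterion can offset or reverse the shift.

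**Conclusion.** The defect lies in the definition and its attribution. ETNA major bleeding differs from both comparators in two respects that act in opposite directions. One of these is unmarked, and the wording carries the same source footnote as PREFER's conflicting wording. This does not fit the claims of close matching and comparability, and the 12-month visual comparison of major bleeding is not like for like.

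Neither direction nor size can be derived from the documents. The −0.9 to +0.3 point range rests wholly on assumed values of R, f and g. Net understatement in ETNA is possible if transfusion-only bleeds outnumber haematocrit-only bleeds, but it is not established. Whether ETNA departs from ISTH 2005 cannot be settled without that source. What is certain is that the ETNA and PREFER wordings cannot both reproduce it in full.

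**What to change.** 1. Reconcile the ETNA cell of Table 2 with footnote b, Objectives and outcome measures, Definitions and the Discussion. Either add transfusion of at least 2 units to the classification of bleeding events, or label the ETNA definition as modified ISTH. In either case, mark the haematocrit criterion as a difference.
2. For the PREFER and Hokusai displays, tabulate 12-month ETNA-VTE major bleeding under the common definition: fatal, critical site, haemoglobin fall of at least 2 g/dL, or transfusion of at least 2 units, without haematocrit. Recount CRNM to match. This corrects only the boundary with major bleeding, since Table 2 also bolds other differences in the comparators' CRNM definitions.
3. If transfusion units are not already captured, query them for reported overt bleeds and collect them from then on. Recruitment was still under way when the article was written.

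The cost is a small query burden, some wording changes and one extra tabulation. The reported major-bleeding rate may change slightly in either direction. The planned sample size does not change.
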